## Abstract

**Background:**

People with intellectual disabilities (ID) have lower levels of physical activity and quality of life and they have a lot of barriers to face when taking part in physical activity. Other problems are the poor adherence to physical activity such people have so this study is designed to improve adherence to physical activity for people with intellectual disabilities with the assistance of an application for smartphones. The aim of the study will be to improve physical activity and physical condition after multimodal intervention and to analyse the promotion of adherence to physical activity through a multimodal intervention and an app intervention (mHealth) in people with ID.

**Methods:**

A two-stage study will be conducted. In stage 1 a multimodal intervention will take place will be done with physical activity and educational advice over eight weeks, two days a week. Data will be measured after and before the intervention. In stage 2 a randomized controlled trial will be conducted. In the intervention group we will install an application to a smartphone; this application will be a reminder to do a physical activity and they have to select whether they have or haven’t done a physical activity every day. This application will be installed for 18 weeks. Data will be measured after and before the application is installed in two groups. We will measure results 10 weeks later when the two groups don’t have the reminder. The principal outcome used to measure the adherence to physical activity will be the International Physical Activity Questionnaire; secondary outcomes will be a fun-fitness test and self-report survey about quality of life, self-efficacy and social support. Samples will be randomized by sealed envelope in two groups, with approximately 20 subjects in each group. It’s important to know that the therapist will be blinded and won’t know the subjects of each group.

**Discussion:**

Offering people with ID a multimodal intervention and tool to increase the adherence to a physical activity may increase the levels of physical activity and quality of life. Such a scheme, if beneficial, could be implemented successfully within public health sense.

**Trial registration:**

ClinicalTrials.gov Identifier: NCT01915381.

## Background

About 1.5% of the adult population have intellectual disabilities (ID), and in over half of these cases the cause of this problem is unknown and this number is higher in developing countries [1]. People with ID have a low level of healthy lifestyle, poor dietary habits and low physical activity (PA). The latter may be due to the number of barriers they face in doing a physical activity and to the few resources and opportunities open to them [2]. However, currently awareness of the barriers and facilitators for people with ID which enable them to take part in physical activity is poor [3] so we find health problems like obesity or chronic disease in this population [4]. People with ID have a poor maintenance in physical activity and it’s important to try to help them to improve this maintenance [5]. In people with ID we find lower levels of physical fitness compared with the general population [6].

Physical activity provides many benefits to people with intellectual disabilities [7] helping to reduce the risk of hypertension, coronary heart disease, stroke, diabetes, breast cancer and colon cancer, depression and falls, and is a key to energy balance and weight control [8]. Most studies use physical intervention to improve physical activity and physical condition, but it is critical that this intervention will be a multimodal intervention (intervention with physical activity and educational advice) [9]. In the bibliography we only found studies that try to improve adherence to the physical activity, but these studies only use physical intervention, not multimodal intervention with educational advice. Most studies use physical intervention to improve physical activity and physical condition, but it is critical that this intervention is a multimodal intervention (an intervention that combines PA and educational advice) [9]. This study should be relevant, because in our opinion this study is the first long-term study to promote PA in people with ID that uses a multimodal intervention, and other authors confirm that studies to promote PA in people with ID are needed because these people face many barriers when they want to practice PA [10,11]. Another problem that we have found is the poor adherence to PA [5], because there are few studies that measure long-term adherence. As a consequence, in our study we expect to improve this adherence through an application for mobile phones where people with ID will have a reminder every day, and results will be measured to ascertain whether a reminder can change the outcome and increase adherence. Nowadays, there are studies that use TICs to improve adherence to a treatment by patients and the results of these studies have been positive [12,13]. We also found a study similar to ours, but the sample studied wasn’t of people with ID; in this study they used an app versus traditional methods to compare self-monitoring in physical activity [14]. To our knowledge there isn’t an app to improve adherence to PA in people with ID, however, an app development for this, and tested in an RCT, may determine whether the expected effect of the multimodal intervention improves adherence with the assistance of the app. The present study will have two aims: the first is to improve physical activity in people with ID after multimodal intervention, and the second is the promotion of adherence to physical activity through an app intervention (mHealth) for people with ID. The hypothesis of our study is to check whether the reminder from the smartphone improves adherence to physical activity in people with ID after multimodal intervention.

## Method/Design

### Design

A two-stage study will be conducted. In stage 1 a prospective study will be conducted. Data will be measured after and before the intervention. In stage 2 a randomized controlled trial will be conducted.

### Participants

Forty people with a mild to moderate level of ID and ranging in age from 18 to 65 will be recruited from an occupational centre (ASPROMANIS, Malaga, Spain). They must be able to read and write in order to answer the questions, they need to be capable of installing the reminder on their smartphone, and they must not be suffering from any disease that will prevent them from undertaking a physical activity.

Before starting the investigation we have guaranteed participants the protection of confidential information obtained from them [Law 15/1999 Protection of Personal Data]. Informed consent was obtained from all subjects, and study procedures were consistent with the Helsinki declaration. The Faculty of Health Sciences Research Committee approved this protocol (UMA-01-13).

### Procedure

For multimodal intervention (stage 1), we have to divide the sample into three working groups, with around 13 people in each group for a low ratio. This intervention will be carried out over eight weeks, twice a week. For the reminder app intervention (stage 2), we will divide the sample into two groups, the assignment of subjects in each group is through a system of sealed envelopes; in this way we will have one group that will have the app reminder on their smartphone and another group that will not. The drop-out of participants in stage 2 will be counted (Figure 1).

**Figure 1 F1:**
[figure not shown]
Flow chart of the study.

### Intervention

All subjects receive a multimodal intervention consisting of a program with an educational approach and physical activity, where a therapist advises on the benefits of PA [15]. Multimodal intervention will be carried out in ASPROMANIS 2 hours weekly over eight weeks. In each session the therapist will provide educational advice brochure [15] with the physical activity to improve strength, flexibility, balance and aerobic condition. Variables will be measured before and after intervention.

Below we separate the sample into two groups, where one group have a reminder on their smartphone and another group are the control group; a researcher by means of a sealed envelope will do assignment to the groups; the therapist will be blinded and will not know what subjects are in each group. The smartphone-based application group will have a reminder find out whether they have done PA every day; in this app this group will have to select whether they have or haven’t done a physical activity.

After 18 weeks, results will be measured to ascertain the adherence in the smartphone group (SG) and the no-smartphone group (NSG, and we will learn whether the reminder has realized the expected effect by comparing the results between both groups. Ten weeks after the reminder has been removed, we will measure the results in the SG and the NSG again, to establish whether the SG continue their adherence to PA and compare this to the NSG.

### Outcome measures

Summary of tools and variables of the study are shown in the Table 1.

**Table 1 T1:** Summary of tools and variables of the study

**Name**	**Measure**	**Variable type**
**IPAQ**	Physical Activity	Main
**Accelerometer Gt3x**	Physical Activity	Secondary
**WHOQoL-DIS**	Quality of life	Secondary
**Barthel**	Level of dependence	Secondary
**FunFitness**	Physical Condition	Secondary
**SE/SS AID**	Social support and autoefficacy	Secondary
**Raven´s progressive matrices**	IQ	Secondary
**Open Interview**	Barriers and facilitators to physical activity	Secondary

#### Secondary outcome measures

We will use accelerometers to measure PA too, because *accelerometers* have previously been found to reliably measure the PA of adults with ID [20]. In our study we will use Actigraph GT3X. A selected group of participants will wear Actigraph for a week to measure PA and this will provide us with more information about the PA of that sample.

To measure physical condition we also to review the *Fun*-*fitness programme test*, Special Olympics; with this programme we can learn about the physical condition of the patients and help them with suggestions on how to improve their physical condition and to avoid injuries. When this test is performed, all participants receive information about their physical profile, and recommendations on how to increase their physical qualities. (http://www.specialolympics.org). In our study we will measure 13 items which cover strength, aerobic condition, balance and flexibility in the sample –for more details see Cuesta-Vargas et al. 2011 [21]. There is also another scale to establish physical condition: this is the FunFitness battery test with nine physical test, developed in another study by Cuesta-Vargas et al. 2013 [22], but we will use the 13 items FunFitness scale because it is fuller.

*Self-report outcome measures* will be used to measure quality of life using the *WHOQoL scale*[23] because this is the scale most recommended by WHO to measure QoL, and because the sample of our study are people with ID, and in this scale they have to answer 12 items in which there are only three possible answers (1, 2 and 3). This scale has also been used in other studies to measure QoL in people with ID in Spain [24]. Reliability of the original version of WHOQol scale was α Cronbach 0.90 [25]. To measure the level of dependence we will use the *Barthel index*; this index provides us quantitative information about the level of dependence, measuring the execution of ten daily life activities [26] (α Cronbach 0.86-0.92) [26]. For social support and self-efficacy for leisure activity we will use the self-efficacy/social support for activity for persons with intellectual disability scale (SE/SS-AID) [27]. In this scale the sample have to answer six self-efficacy items and 17 social support items with three possible answers. Reliability of SE/SS AID is (α Cronbach 0.70-0.74) [28]. We will use a questionnaire about socio-demographic data, with gender, age, level of study, birthplace and associated diseases.

### Statistical treatment

Mean and standard deviations or 95% confidence intervals of the values will be calculated for each variable. Pre-intervention values prior to each condition will be compared using the independent t-tests for continuous data. A 2x2 mixed model ANOVA with supplementation (SG or NSG) as the between-subjects variable and time (pre-; post-intervention) as the within-subjects variable will be used. The hypothesis of interest was intervention * time interaction. The Bonferroni test will be used for post hoc analysis. A P-value < 0.05 was considered statistically significant. Data will be analysed using the SPSS package (version 19.0).

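### The only stated outcome model has two time levels, so the planned smartphone versus no-smartphone comparison ten weeks after removal of the reminder has no stated analysis

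*Protocol article*

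**What the plan says.** **Model.** The Statistical treatment section specifies "A 2x2 mixed model ANOVA with supplementation (SG or NSG) as the between-subjects variable", followed by "time (pre-; post-intervention) as the within-subjects variable will be used". The target of inference is given as "The hypothesis of interest was intervention * time interaction". The group labels tie this model to the randomised stage 2.

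**Other procedures in that section.** These are descriptive statistics for each variable, independent t-tests of pre-intervention values, and one sentence on multiplicity: "The Bonferroni test will be used for post hoc analysis". No contrasts are named for it.

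**Measurement times.** The Methods part of the abstract says of stage 2: "Data will be measured after and before the application is installed in two groups". It sets the app period at 18 weeks and adds a measurement 10 weeks later. The Intervention section repeats the later visit: "Ten weeks after the reminder has been removed, we will measure the results in the SG and the NSG again". It gives that visit its own purpose: "to establish whether the SG continue their adherence to PA and compare this to the NSG".

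**The concern.** The post-removal visit is the only evidence the trial will have on whether any effect outlasts the reminder. The article presents the trial as long-term and notes how few studies measure long-term adherence. The visit also supports a randomised comparison, because both groups are measured again.

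The article does more than leave this comparison undescribed. It fixes the design as 2x2 and lists the two time levels, and that conflicts with the three-time schedule in its own Intervention section. An analyst following the text would not test the persistence question. An analyst who wished to test it would have to choose the model and contrast later, possibly with the data in view.

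**Working it through.** The check is a count of measurement times against model levels. No figure stated in the article depends on it, so there is none to reproduce.

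**1. Stage 2 times against the model**

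| Stage 2 measurement | Source | Level in the 2x2 model |
|---|---|---|
| Before the app | Abstract (Methods) | pre |
| 18 weeks, end of reminder | Abstract (Methods); Intervention | post-intervention |
| 10 weeks after removal (18 + 10 = week 28) | Abstract (Methods); Intervention | none |

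Three times are measured and two are modelled. Of the two post-baseline group comparisons, one is covered.

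**2. Which visit is the post level?** The label could be applied to either later visit, so it was checked elsewhere. The Intervention section says that the 18-week between-group comparison will show whether the reminder had its expected effect. The Primary outcome measure section rests the principal outcome on IPAQ data from before and after the reminder. Both point to pre-app versus 18 weeks, so the primary comparison is in the model.

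**3. Does anything else in Statistical treatment cover week 28?**
- Means with SDs or 95% confidence intervals could be reported at that visit, but no group comparison is specified for them.
- The t-tests are limited to pre-intervention values.
- A 2x2 model has four cells: SG and NSG, each at pre and at post. A post hoc contrast of that model combines those four cells, and none is a follow-up cell.

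**4. What including the third time changes.** With G groups, T times and N completers, the interaction has (G - 1)(T - 1) numerator and (N - G)(T - 1) error degrees of freedom. Taking N = 40, the planned recruitment with no losses:
- 2x2: (1)(1) = 1 and (38)(1) = 38.
- 2x3: (1)(2) = 2 and (38)(2) = 76.

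The 2x3 interaction is therefore a joint test over both later visits. It does not isolate either one, so the 18-week and week-28 contrasts must be named.

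**5. Why a fixed order rather than an alpha split (illustration).** Assume d = 1 at both visits, as in the sample size section, and a two-sided two-sample t-test; the article does not state sidedness. Power comes from the noncentral t distribution with 2n - 2 degrees of freedom and noncentrality d x sqrt(n/2).

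| n per group | Noncentrality | Power, alpha 0.05 | Power, alpha 0.025 |
|---|---|---|---|
| 15 | sqrt(7.5) = 2.74 | 0.75 | 0.65 |
| 20 | sqrt(10) = 3.16 | 0.87 | 0.79 |

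Splitting alpha equally would cost 8 to 10 percentage points of power per contrast. Testing week 28 only after week 18 leaves the primary test at 0.05.

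**The case against.** The strongest reply is that persistence is subsidiary. The Background gives two aims and one hypothesis, and none mentions what happens after removal. The stated model fits the primary question, and detail on a later visit is often left to a fuller document that is not shown here. This stands as a limit on the size of the point. It does not remove it, because the article states a two-level model that its own schedule contradicts, and a fuller document could include the visit only by departing from that text.

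Four stronger readings are tempting, and the documents do not support them:

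- *Nothing says which visit decides.* The Intervention and Primary outcome measure sections tie the deciding comparison to 18 weeks.
- *The false-positive rate is inflated by two looks.* That needs a rule under which success at either visit counts. No such rule is written, and the later visit has a different question.
- *The Bonferroni sentence is empty in a 2x2 design.* It can apply to simple effects after an interaction, such as group at each time and time within each group. It is under-specified, and it does not reach week 28.
- *The third measurement is discarded.* The article plans to collect and compare it. What is missing is a model for that comparison.

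**Conclusion.** The stated model does not fit the stated design at one point. The group comparison ten weeks after removal is planned, has its own purpose, and is in no stated inferential analysis. The defect is confined to this secondary persistence question; the comparison from pre-app to 18 weeks is covered by the 2x2 model.

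The conclusion rests on reading the post level as the 18-week visit, which two other sections support. It does not depend on the sample size calculation or on any assumed effect; the power figures above bear only on the choice of remedy.

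**What to change.** Replace the 2x2 sentence with one model that includes both post-baseline times. One sound option is a repeated-measures mixed model for IPAQ at weeks 18 and 28, with group, time, group by time, and pre-app IPAQ as covariate. It can also use participants who miss one of the two later visits, which is useful since the article expects to count drop-outs. A 2x3 mixed ANOVA (pre-app, week 18, week 28) with named contrasts would close the gap too.

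Then state:

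1. The group difference at 18 weeks is the single primary test, confirming what the article already implies. If pre-app IPAQ becomes a covariate, reword the hypothesis sentence, because the primary effect is then the adjusted week-18 difference and no longer the interaction.
2. The group difference at week 28 is a secondary contrast, tested after the primary one.
3. Any Bonferroni adjustment may stay for other post hoc contrasts, provided they are named.

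The cost is analysis wording. No visits, data or participants are added.

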### Sample size calculation

A priori sample size calculation for stage 2 indicated 15 patients per group were required in order to detect a significant difference of 25% in IPAQ [29] between the intervention and control group (Effect size d = 1, alpha = 0.05, beta = 0.08).

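### Stage 2 sample size: 15 per group with d = 1 and two-sided alpha 0.05 gives about 75% power, not the 92% that the stated beta of 0.08 implies

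*Protocol article*

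**What the plan says.** The Sample size calculation section of the protocol article states that "15 patients per group were required in order to detect a significant difference of 25% in IPAQ", for a comparison "between the intervention and control group". The inputs follow in brackets: "Effect size d = 1, alpha = 0.05, beta = 0.08". The section gives no sidedness, standard deviation, pre-post correlation or dropout allowance.

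The Statistical treatment section plans a 2x2 mixed ANOVA of group by time, with the interaction as the hypothesis of interest. Its significance criterion is "A P-value < 0.05 was considered statistically significant", again without sidedness.

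The abstract describes randomisation into two groups "with approximately 20 subjects in each group", and the Participants section gives forty people in all. Planned recruitment is therefore larger than the calculated requirement.

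**The concern.** The sentence gives an effect size, an alpha, a beta and a resulting sample size, so it can be checked from the article alone. The sample size does not follow from the inputs. This is a wrong statement and not a detail left to a fuller document.

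It is the only sample size justification the article gives for the randomised stage, and it concerns the primary outcome. A reader who takes the beta at face value believes that a true effect of d = 1 would be missed 8% of the time. On the default reading the figure is about 25% with 15 per group and about 13% with 20. A non-significant result would then look like stronger evidence against the reminder than it is.

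**Working it through.** **Inputs from the Sample size calculation section.** n = 15 per group, d = 1, alpha = 0.05, beta = 0.08 (power 1 − 0.08 = 0.92), two independent groups. From the abstract: about 20 per group. Sidedness is not stated, so both cases are shown, with two-sided as the default.

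**Step 1. Try to reproduce 15 per group (normal approximation).** n per group = 2 × (z_alpha + z_power)² / d².

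- Two-sided, 92%: 2 × (1.960 + 1.405)² = 22.6, so 23.
- One-sided, 92%: 2 × (1.645 + 1.405)² = 18.6, so 19.
- Two-sided, 80%: 2 × (1.960 + 0.842)² = 15.7, so 16.
- One-sided, 80%: 2 × (1.645 + 0.842)² = 12.4, so 13.

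None of these gives 15.

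**Step 2. Exact two-sample t-test.** Power comes from the noncentral t distribution with 2n − 2 degrees of freedom and noncentrality d × √(n/2). At n = 15 there are 28 degrees of freedom, the noncentrality is √7.5 = 2.739 and the two-sided critical value is 2.048.

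| n per group | Power, two-sided | Power, one-sided |
|---|---|---|
| 15 | 75.3% | 84.8% |
| 17 | 80.7% | 88.6% |
| 20 | 86.9% | 92.8% |
| 24 | 92.4% | 96.1% |

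The smallest n per group is:

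- for 92% power: 24 two-sided, 20 one-sided;
- for 80% power: 17 two-sided, 14 one-sided.

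Again no case gives 15. At 15 per group the two-sided beta is 1 − 0.753 = 0.247, about three times the stated 0.08 (0.247 / 0.08 = 3.1). The normal approximation gives 78.2% power at 15 per group, so the choice of method does not explain the gap. For 15 per group to give 92% two-sided power, d would have to be about 1.27.

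**Step 3. The planned interaction test.** In a 2x2 mixed ANOVA, the group-by-time test is equivalent to a two-sample t-test on the pre-post change.

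- If d = 1 is defined on the SD of the change, the figures in Step 2 apply unaltered.
- If d = 1 is defined on the raw IPAQ SD (equal before and after), the SD of the change is √(2(1 − r)) raw SDs, where r is the pre-post correlation. The effective size is then 1 / √(2(1 − r)).

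The article gives no r, so the values below are an assumed range (two-sided alpha 0.05):

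| r | Effective d | Power, 15 per group | Power, 20 per group |
|---|---|---|---|
| 0 | 0.707 | 46% | 59% |
| 0.3 | 0.845 | 61% | 74% |
| 0.5 | 1.000 | 75% | 87% |
| 0.6 | 1.118 | 84% | 93% |
| 0.7 | 1.291 | 93% | 98% |

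Under this scaling, 15 per group reaches 92% only at r of about 0.69.

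**The case against.** Four points can be made for the plan.

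1. *Beta of 0.08 may be a slip for 0.20, or for a power of 0.8.* This is the likeliest explanation: 80% power two-sided gives 15.7 before rounding up, within one or two participants of 15. It explains the sentence but does not save it. The printed beta would still be wrong, and 15 per group would still fall short of 80% two-sided (75%, or 78% by normal approximation).

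2. *The planned test is the interaction, which can gain from repeated measures.* This stands as a limit on the finding. A pre-post correlation of about 0.69 with d on the raw SD would give 92% at 15 per group. The article states no such correlation and describes the effect as a difference between groups. Below 0.5 the same scaling makes power worse than 75%. So 0.25 is the beta for a specified test, and a reader should not take it as the trial's one true type II error.

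3. *About 20 per group are planned.* This also stands, and it limits the consequences. A reader might infer that the stated beta is missed at 20 per group as well. That is so for two-sided testing (86.9%, beta 0.131), but one-sided testing at 20 per group gives 92.8%, and the article does not state sidedness. Two-sided is the reasonable default, though it is an assumption.

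4. *The match between a 25% IPAQ difference and d = 1 may be documented elsewhere.* A reader might infer that the trial is far weaker still, because d = 1 would require an SD of only 25% of the mean if the 25% is relative to the mean. The article does not support that step. It attaches a cited source to the 25% figure, the SD may be given there or in the full protocol, and any other SD would be invented for the purpose.

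**Conclusion.** The point holds as an inconsistency within one sentence. With d = 1 and alpha 0.05, 15 per group does not give a beta of 0.08 in a two-group comparison: power is about 75% two-sided or 85% one-sided, against 92% implied, and 92% needs 24 or 20 per group respectively. Reading the beta as a slip for 80% power narrows the gap to one or two participants in two-sided testing without closing it.

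These figures rest on a two-sample t-test with equal groups, complete data and d scaled to the score analysed. For the interaction with d on the raw score, power cannot be fixed without a pre-post correlation.

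Severity is moderate. Planned recruitment already exceeds the stated requirement, so the power is misstated but the design does not fail. The documents do not show that the trial is badly underpowered.

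**What to change.** Keep the 40 participants, delete the beta of 0.08, and replace the sentence with one that names the test, for example:

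*For a two-sided two-sample comparison at alpha 0.05 with d = 1, where d is defined on the SD of the analysed score (the pre-post change, for the group-by-time interaction), power is 87% with 20 per group and 75% if 15 per group remain.*

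If d was meant on the raw IPAQ SD, state the pre-post correlation assumed and quote the matching power: at 20 per group 59% for a correlation of 0, 74% for 0.3, 87% for 0.5 and 93% for 0.6.

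The cost is one corrected sentence and, on the default two-sided reading with d on the analysed score, a lower stated power. Recruitment, allocation and analysis do not change.
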